### Randomisation

A computer-generated list of random numbers will be used to create a series of numbered, sealed opaque envelopes containing assignments to either placebo or supplementation with *B. infantis*. For every three infants assigned to *B. infantis* supplementation, two additional infants will be assigned to placebo. The study pharmacist will be responsible for the randomisation and delivery of the blinded supplements.

## Study methods and interventions

### Infant stool collection

Parents will be instructed how to collect and store infant stool samples at home. Stool samples will be collected twice weekly for the first 6 weeks of life then once weekly at weeks 24, 36, 52, and 78. If breastfeeding is discontinued at any point, an additional series of weekly stool samples will be collected for 6 weeks following discontinuation. At the initial enrollment visit parents will be provided with a stool sample collection including a sealable freezer box, marked sealed collection tubes and sealable plastic bags. Parents will be instructed to store samples in their home freezers immediately after collection to prevent secondary bacterial growth, and discard any samples not able to be frozen at the time of collection. Stool samples will be stored in the home freezers of study participants and picked up by study personnel once weekly to ensure they can be properly transported to the laboratory under temperature-controlled conditions. Any samples that are not stored immediately in the freezer at the time of collection or thaw en route to the laboratory will be discarded and parents will be instructed to collect and store a new stool sample according to the protocol. The stool samples will be analysed in the laboratory using DNA extraction to determine the identity and predominance of various commensal bacterial species, including the percentage of *B. infantis* present. The method of stool collection that will be provided to parents is described below:At any time of day, scoop 1–2 teaspoons of your infant’s stool with the tongue depressor into the sealable collection tube. The amount of stool should fill the tube between the 5 and 10 ml mark.Seal the tube and label with the time and date it was collected.Place the stool filled tube inside a sealable plastic bag and seal it.IMMEDIATELY place the sealed bag containing the stool sample into the study freezer box and store it in your freezer. It is important that stool samples are stored in the freezer immediately after collection to prevent bacteria from growing. If the stool sample was not immediately placed in the freezer, please discard the sample and collect another sample from your baby at the earliest convenience.

### Breast milk collections

Mothers will collect a series of breast milk samples for laboratory analysis to determine the type and proportion of milk oligosaccharides present at various time points. The purpose of this analysis is to allow correlation of the type and amount of milk glycans present in breast milk with that in the infant stool samples, both to verify the presence of the specific oligosaccharides preferred by *B. infantis* as well as to determine if appropriate amounts are present in the infant stool to represent exclusive breastfeeding practices.

Breast milk will be collected at 7, 14, 42, 120, and 180 days after the birth of the infant, and stored in the home freezers in the same manner as the stool samples. Parents will be provided with detailed instructions and supplies for collection as described below:Between 2–4 hours after your last breastfeeding, use the breast pump to pump all the milk from one breast into the breast pump collection bottle.Using the measuring cup, measure out 12 ounces of breast milk.Divide the 12 ounces of breast milk into three (3) collection tubes, with four (4) ounces per tube.Using the collection tube labels and a permanent marker, label each collection tube with the date and time of collection.IMMEDIATELY, place the three tubes of breast milk in a single ziplock bag, seal it, and place in the study collection box stored in your freezer.Wash and dry the breast pump, collection bottle, and measuring cup thoroughly after each use

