## Background

The idea of probiotics, “live microorganisms that when administered in adequate amounts confer a health benefit on the host”, dates back to Elie Metchnikoff who hypothesised over 100 years ago that lactic acid bacilli had health benefits [1]. To date, thousands of reports of probiotics have supported the potential health benefits of these bacteria and the World Health Organization (WHO) has formulated guidelines for their use as nutritional supplements as well as investigation into their potential therapeutic properties [2]. Probiotics have been studied for the treatment and prevention of a variety of diseases in children including atopic dermatitis, bacterial gastroenteritis, inflammatory bowel disease, and necrotizing enterocolitis [3–5]. Overall, the data concerning probiotics as preventive agents for atopic diseases such as atopic dermatitis and food allergies are inconclusive, with some studies suggesting a possible benefit and others showing mixed results [4, 6–8].

Humans and other mammals are hosts to a diverse set of symbiotic as well as pathogenic intestinal bacteria. Approximately 1000 microbial species reside at a density of 1 × 10^12^ organisms per gram of colonic content [9, 10]. Several studies have demonstrated a clear link between immune system development and the composition of gut microbiota [11–13]. In addition, disruption of intestinal barrier function may lead to premature exposure of the infant to atopy-inducing environmental allergens, which would theoretically predispose the infant to the development of food allergies [14]. By protecting against colonisation by pathogenic bacteria, probiotics may help protect intestinal barrier function and thus decrease the susceptibility for development of atopic diseases and food allergies [15]. However, the pharmacokinetics of commensal bacteria and the dosage required to achieve predominant gut colonisation has thus far not been quantified. The probiotic that will be administered in our proposed phase I clinical trial, *Bifidobacterium longum subsp. infantis (B. infantis),* is unique in that it is able to fully utilise human milk oligosaccharides [16]. Thus, an exclusively breastfed infant’s gut provides the ideal environment to facilitate colonisation with this commensal bacteria [16–18]*.*

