**Fig. 1 Fig1:**
[figure not shown]
A parallel-group, placebo-controlled, randomised, double-blind ascending dose phase I study of dietary supplementation with *B. infantis.* Groups of healthy infants will receive increasing doses of *B. infantis* until it comprises 50 % of their gut microbiota, defined as the pharmacologically effective dose (*ED*). This figure arbitrarily designates Group 6 as receiving the ED of *B. infantis*. After the ED has been reached, two additional dose escalations will occur to determine the impact that additional *B. infantis* has on the gut microbiota. To satisfy Hanley’s Rule of Three, 30 infants will receive the highest dose of *B. infantis*. “*X*” represents the maximum recommended starting dose (*MRSD*). A modified Fibonacci Series (X, 2X, 3X, …) is used to guide the dose escalations. *CFU* colony-forming units

Study visits will be scheduled for weeks 1, 2, 6, 24, 36, 52, and 78. Parents will complete surveys at each study visit to monitor the infants for potential adverse events associated with probiotic administration including feeding intolerance, fevers, or bowel irregularities including constipation and diarrhoea.

Stool samples will be collected twice weekly for the first 6 weeks of life then once weekly at weeks 24, 36, 52, and 78. Stool samples will be analysed to determine the relative abundance of *B. infantis* over time, and the overall diversity of the gut microbiota with and without *B. infantis* supplementation. Stools will also be analysed for milk oligosaccharides to verify consumption of breast milk and to correlate the proportion of human milk oligosaccharides and free sugar monomers seen in the infant stool at various levels of *B. infantis* colonisation.

Breast milk will be collected at 7, 14, 42, 120, and 180 days after the birth of the infant to determine the type and proportion of milk oligosaccharides present at various time points. The purpose of this analysis is to allow correlation of the type and amount of milk glycans present in breast milk with that in the infant stool samples.

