### Secondary outcome measures

#### Milk oligosaccharide consumption

All stool samples will also be analyzed for the presence of oligosaccharides unique to breast milk and for the presence of free saccharide monomers, which are products of their incomplete digestion. *B. infantis* abundance will be correlated to these values.

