The pharmacokinetically guided design of this proposed phase I trial has not been attempted in prior probiotic studies. If successful the trial will identify a pharmacologically effective dose (ED) and maximum effective dose (MaxED) for *B. infantis* supplementation in healthy infants. The next generation sequencing strategy that will be employed to analyse the stool of the infants to determine gut colonisation with *B. infantis* has been well standardised, and is a common method for analysis of gut microbiota. Infants will also be monitored closely for potential adverse effects in case a maximally tolerated dose (MTD) is reached during the ascending dose study. The design of the trial is also innovative because the specific probiotic used for the supplementation will have a competitive advantage in an exclusively breastfed infant; it is the only bacterium that can fully utilise the complex oligosaccharides in breast milk as an energy source. Thus, the design of the trial provides an optimal environment for *B. infantis* to outcompete other intestinal microbiota. The rationale for the choice of probiotic used in prior infant trials is not clear; however, in this study it is based upon knowledge of the human milk glycome and specific metabolic needs of *B. infantis*. Our ultimate goal is to develop a clinically appropriate, safe, and effective dosing regime for probiotics that may be utilised in further phase II and phase III clinical trials. In doing so, we hope to lay the foundation for the design of objective, standardised clinical trials to assess the efficacy of probiotics for the prevention of a variety of diseases, including atopic dermatitis and food allergies in at-risk infants.

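### The amount of milk oligosaccharide in stool cannot verify exclusive breastfeeding, because the study organism is expected to consume it

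*Protocol article*

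**What the plan says.** Stool oligosaccharides have two uses in the protocol article.

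- **Feeding check.** Breast milk collections compares glycans in the mother's milk with those in the infant's stool, in part to "determine if appropriate amounts are present in the infant stool to represent exclusive breastfeeding practices". Study design, in the text after Fig. 1, has a weaker form: "Stools will also be analysed for milk oligosaccharides to verify consumption of breast milk".
- **Consumption outcome.** The same Study design sentence goes on "to correlate the proportion of human milk oligosaccharides and free sugar monomers seen in the infant stool at various levels of" *B. infantis* colonisation. Under Secondary outcome measures, Milk oligosaccharide consumption, the article states: "All stool samples will also be analyzed for the presence of oligosaccharides unique to breast milk". It adds free monomers and says that *B. infantis* "abundance will be correlated to these values".

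The biological premise appears twice. The Background says the organism "is unique in that it is able to fully utilise human milk oligosaccharides", and the Discussion says "it is the only bacterium that can fully utilise the complex oligosaccharides in breast milk as an energy source".

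Exclusive breastfeeding matters because the intention to do so for at least 6 months is an entry condition, and because it is the stated reason to expect colonisation.

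**The concern.** A check on a required exposure should not itself be changed by the treatment. Here it is expected to be: what remains in stool is what the infant took in, less what gut bacteria removed. If *B. infantis* removes these sugars as the article says, an infant in whom supplementation works can show the low value that the check would read as departure from exclusive breastfeeding.

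Two things are at stake. One is the feeding verification, which is weakest in well-colonised infants. The other is the planned correlation of abundance with stool oligosaccharides: if intake is judged from the same variable that serves as the consumption outcome, a low value can be read either way.

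**Working it through.** **Step 1: what each stool result can mean on the article's premises**

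| Stool oligosaccharide | Possible explanations | Settles exclusivity? |
|---|---|---|
| Low | Little breast milk, or breast milk taken and consumed by *B. infantis* | No |
| High | Breast milk taken and not consumed; formula may or may not have been added | No |
| Detected at all | Some breast milk was taken, since the assay targets sugars unique to it | No, but valid evidence of some intake |

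Only the last row supports a feeding statement, and it is the Study design use (some intake), not the Breast milk collections use (exclusivity from the amount).

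**Step 2: is there a figure to reproduce?** No. The article gives no stool cut-off, no depletion rate and no between-infant spread. Steps 3 and 4 are therefore illustrations on assumed values. They show direction and range and do not estimate the effect.

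**Step 3: intake and colonisation trade off.** Assume the expected stool level is proportional to f × (1 − u·a). Here f is the share of intake that is breast milk, a is the *B. infantis* share of the microbiota, and u is the share of oligosaccharide removed per unit of a. A fully breastfed infant (f = 1) at a = 0.50 has the same expected level as a poorly colonised infant (a = 0.05) with f = (1 − 0.50u)/(1 − 0.05u):

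- u = 0.50: 0.750/0.975 = 0.77
- u = 0.80: 0.600/0.960 = 0.63
- u = 0.95: 0.525/0.9525 = 0.55

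At the colonisation level that defines the effective dose, full breastfeeding thus looks like breast milk making up 55 % to 77 % of intake in a poorly colonised infant.

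**Step 4: false flags among infants who are all exclusively breastfed.** Add lognormal spread with log-scale SD s, and set the cut-off at the 5th centile of breastfed infants with a = 0.05. Then

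P(flag | a) = Φ{[ln(1 − 0.05u) − 1.645s − ln(1 − u·a)]/s}.

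- Highest case at a = 0.50 (u = 0.95, s = 0.3): (−0.0487 − 0.4935 + 0.6444)/0.3 = 0.34, so P = 0.63.
- Lowest case at a = 0.50 (u = 0.50, s = 0.8): (−0.0253 − 1.3159 + 0.2877)/0.8 = −1.32, so P = 0.09.

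| s | u | a = 0.05 | a = 0.30 | a = 0.50 | a = 0.70 | a = 0.90 |
|---|---|---|---|---|---|---|
| 0.3 | 0.50 | 5 % | 12 % | 22 % | 39 % | 60 % |
| 0.3 | 0.95 | 5 % | 25 % | 63 % | 97 % | 100 % |
| 0.5 | 0.80 | 5 % | 12 % | 24 % | 47 % | 79 % |
| 0.8 | 0.50 | 5 % | 7 % | 9 % | 13 % | 18 % |
| 0.8 | 0.95 | 5 % | 10 % | 18 % | 37 % | 76 % |

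In every scenario run (s of 0.3, 0.5 and 0.8; u of 0.50, 0.80 and 0.95) the false-flag rate rises with colonisation. How far it rises depends wholly on the assumed values.

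**The case against.** Several points against the concern have force.

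- **The effective dose.** A reader might infer that successful infants would be removed and the effective dose read too high. Withdrawal of subjects does list protocol non-compliance as a possible reason for removal, and with three active infants per dose level one removal would take a third of that level's active data. But nothing there mentions feeding or this assay, and no section sets a cut-off or drops anyone on it. Study design points the other way: infants whose mothers stop breastfeeding are kept and give six further weekly samples. The effective dose is read from 16S sequencing at 6 weeks. The inference is not supported.
- **Bias by dose.** This too goes beyond the text. The article states what the organism can metabolise, not what is left in stool. Whether colonisation rises with dose is what the trial is to find out, and the design allows for a dose above which it does not rise further. The supported statement is conditional.
- **Other data help.** Free monomers are assayed, described as "for the presence of free saccharide monomers, which are products of their incomplete digestion". Microbiota and oligosaccharides are measured in the same weeks (Table 2), mothers' milk is sampled on five days, and two infants in five receive placebo. Low oligosaccharide with little *B. infantis* does not suggest consumption. This eases the ambiguity but does not remove it in highly colonised infants. Full utilisation would leave few monomers, and maternal milk shows what was available, not what was drunk.
- **The article is condensed.** The full protocol's survey forms may already hold a feeding question, so its absence here is not the point. The point is that the article itself names the stool amount as a test of exclusivity.

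**Conclusion.** The concern stands as a fault in how exclusivity is verified. On the protocol's own account of the organism, the stool amount depends on both intake and colonisation. It therefore cannot establish exclusive breastfeeding, and it is least reliable in infants above the 50 % level the trial aims for. The error may differ by arm or dose if colonisation does.

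The harm is limited to the feeding verification and to interpretation of the oligosaccharide–abundance correlation. That correlation is harder to interpret without a separate intake measure, but the paired data keep it from being uninterpretable. The effective dose is untouched unless infants are dropped or reclassified on this marker.

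The direction rests on one premise, that *B. infantis* consumes these sugars in the gut as the article says. The size is unknown: the 9 % to 63 % at 50 % colonisation comes from assumed depletion, spread and cut-off, and at its low end the change from 5 % is small. The point merits correction; it does not undermine the primary endpoint.

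**What to change.** - In Breast milk collections, stop inferring exclusivity from the stool oligosaccharide amount. Keep the maternal milk analysis to confirm that the relevant substrate is present.
- Record a dated parent report of feeding since the last sample (breast milk only, any formula, other food) at the existing stool collections, weekly pick-ups or surveys. Use it as the measure of exclusivity and as the intake variable when interpreting the correlation.
- In Study design, keep detection of breast-milk-specific oligosaccharides, but only as positive evidence of some breast milk intake. State that a low value is not read as non-breastfeeding.
- Keep stool oligosaccharides and free monomers as the consumption outcome.

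The cost is one short question at contacts that already take place, plus a wording change. If the full protocol's forms already ask it, only the wording changes. Trial status says recruitment has not begun, so no data would be affected. The downside is that parents may overstate exclusivity. Because participants and investigators are blinded, that error should not track what the infant was assigned, whereas the stool marker's error may.

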Entry into the study requires the intent to breastfeed exclusively for a minimum of 6 months. If mothers decide to discontinue breastfeeding during the study, we will note that in the infant’s notes and obtain an additional series of weekly stool samples for 6 weeks after discontinuation of breastfeeding. The purpose of this additional stool sample collection is to determine if discontinuation of breastfeeding has an impact on the level of existing *B. infantis* colonisation in the infant gut.

A table of the schedule of study visits and specimen collections is provided in Table 1, and an overview of the timeline of the study interventions and assessments is provided in Table 2.

**Table 1 Tab1:** Schedule of study visits and specimen collections for each infant and mother

Week	Visits and activities
Prior to starting the study	• The patients’ parents or legal guardians will be asked to read and sign the consent form and will be instructed on the procedures for collection and storage of stool samples. They will be asked to refrain from giving the child any other dietary supplementation or probiotics while in the study and to inform the researchers if they are prescribed oral antibiotics at any time during the study.
Week 1	• Initial study visit, adverse event survey administration to parents and administration of first dose of *B. infantis* or placebo on day 7 of life.
	• Week 1 stool samples collected (infants will have stool samples collected twice weekly for the first 6 weeks and then at the study visits at weeks 6, 24, 36, 52, and 78).
	• If breastfeeding is discontinued at any point in the study, an additional series of six weekly stool samples will be collected following discontinuation in addition to the regularly scheduled collections
	• Mother collects breast milk on day 7 of life.
Week 2	• Study visit, adverse event survey administration to parents and administration of second dose of *B. infantis* or placebo on day 14 of life.
	• Week 2 stool samples collected
	• Mother collects breast milk on day 14 of life.
Week 3	• Week 3 stool samples collected
	• Adverse event survey administration to parents
Week 4	• Week 4 stool samples collected
	• Adverse event survey administration to parents
Week 5	• Week 5 stool samples collected
Week 6	• Study visit, adverse event survey administration to parents.
	• Week 6 stool sample collected.
	• Mother collects breast milk on day 42 of life.
Week 17	• Mother collects breast milk on day 120 of life.

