#### Exclusion criteria

Infants given dietary supplementation, including other probiotics.Infants born prior to 34 weeks gestation.Infants below 10^th^ percentile for body weight.Postnatal use of antibiotics (oral, intramuscular, or intravenous) by either the mother or the infant. Of note, prenatal maternal Group B streptococcus prophylaxis is not a criterion for study exclusion.Family history of immunodeficiency syndrome(s).Infants with signs of a clinically apparent underlying immunodeficiency.Intent to use non-breast milk infant formula for feeding during the first 6 months.History of gastrointestinal tract abnormality or infection.

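### The milk collection step asks for 12 ounces from one breast 2–4 hours after a feed, an implausible volume or unit for nearly all mothers

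*Protocol article*

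**What the plan says.** The Breast milk collections section of the protocol article sets out the home procedure as an ordered list.

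- Timing: "Between 2–4 hours after your last breastfeeding".
- Source: "use the breast pump to pump all the milk from one breast into the breast pump collection bottle".
- Volume: "measure out 12 ounces of breast milk".
- Aliquots: "Divide the 12 ounces of breast milk into three (3) collection tubes, with four (4) ounces per tube".
- Days: "Breast milk will be collected at 7, 14, 42, 120, and 180 days after the birth of the infant".

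The order of the steps presupposes that one breast, pumped once, gives at least the volume to be measured out. The list does not mention a lower yield, the second breast, or adding milk from another session.

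The section gives the samples two uses. One is to relate the glycans in the milk to those in the infant's stool. The other is to help judge whether the stool content fits exclusive breastfeeding. Exclusive feeding is a condition of the trial: the Study design section states "Entry into the study requires the intent to breastfeed exclusively for a minimum of 6 months", and the Exclusion criteria list "Intent to use non-breast milk infant formula for feeding during the first 6 months".

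**The concern.** The instruction fixes three things together: one breast, a short interval since the last feed, and a large volume. The first two limit how much milk is available, and the third looks far above that limit. If so, a mother cannot satisfy all three and has to choose which to break.

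She can submit less than was asked. Or she can reach the volume by using both breasts or several sessions. In that case the sample no longer comes from one breast at a known interval after a feed, and samples from different mothers and days are no longer collected alike. At the stated maximum of 90 infants there are 90 × 5 = 450 planned collections, each subject to this choice. What is at stake is the comparability of the milk samples in the glycan correlation and the breastfeeding check. Also at stake is the milk a mother would hold back from her infant on a collection day if she tried to meet the target.

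**Working it through.** **Inputs from the protocol article (Breast milk collections):** 12 oz per collection; three tubes of 4 oz; one breast; 2 to 4 hours since the last feed; five collections.

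**Inputs assumed:** 1 oz = 29.57 mL; equal output from the two breasts; a steady refill rate. The documents do not state total daily output, so it is varied from 400 to 1500 mL.

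**1. The plan's own figure.** 3 tubes × 4 oz = 12 oz, so total and split agree. In metric units, 12 × 29.57 = 354.9 mL per collection and 4 × 29.57 = 118.3 mL per tube.

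**2. Daily output implied by the instruction.** If the pumped breast refilled for *h* hours, output from both breasts = 2 × 354.9 × 24/*h*.

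- *h* = 2: 2 × 354.9 × 12 = 8.5 L/day
- *h* = 4: 2 × 354.9 × 6 = 4.3 L/day
- *h* = 8 (a lenient case in which that breast was skipped at the last feed): 2 × 354.9 × 3 = 2.1 L/day

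**3. Yield of one breast under the assumed range.** Yield = (daily output / 2) × *h*/24; shortfall = 354.9 / yield.

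| Assumed output (mL/day) | Yield at 2 h (mL) | Yield at 4 h (mL) | Shortfall at 2 h | Shortfall at 4 h |
|---|---|---|---|---|
| 400 | 16.7 | 33.3 | 21.3 × | 10.6 × |
| 600 | 25.0 | 50.0 | 14.2 × | 7.1 × |
| 800 | 33.3 | 66.7 | 10.6 × | 5.3 × |
| 1000 | 41.7 | 83.3 | 8.5 × | 4.3 × |
| 1500 | 62.5 | 125.0 | 5.7 × | 2.8 × |

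In the 8-hour case the yield is 66.7 mL at 400 mL/day and 250 mL at 1500 mL/day. The request is still 5.3 to 1.4 times the yield.

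**4. Time one breast would need to make 354.9 mL.** 354.9 / (daily output / 48) gives 42.6 hours at 400 mL/day and 11.4 hours at 1500 mL/day, against the 2 to 4 hours stated.

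**5. Milk taken from the infant, in two separate cases.**

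- A mother who pumps one breast once and stops gives up (2 to 4)/24/2 = 4 to 8 % of a day's milk, whatever her output.
- A mother who pools until she has 12 oz gives up 354.9/400 = 89 % down to 354.9/1500 = 24 % of a day's milk. This second case goes beyond what the text tells her to do.

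**The case against.** The strongest reply is that nothing in the document contradicts the figure. The tube split adds up, and no yield is stated, so implausibility depends on an outside assumption. That stands: this is not an error of addition, and the 4.3 to 8.5 L/day in step 2 looks impossible only to someone who brings an idea of normal output. Residual milk or very high output could close the gap for a few mothers. But the conclusion does not hang on one remembered value. The shortfall persists over the whole range from 400 to 1500 mL/day, and even with eight hours of refill.

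A second reply is that handling details belong in the full protocol or the parent sheet, which an article condenses. That would answer a complaint about something left out. Here the volume is stated, more than once, as part of the instructions parents will receive.

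Three stronger readings are tempting, and the documents do not support them.

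- A reader might infer that the trial's effective dose is put in doubt through loss of exclusive breastfeeding. Under Primary outcome measures, colonisation is determined by 16S sequencing of stool at 6 weeks. Only the day 7 and day 14 collections precede that assessment. A mother who follows the text gives up 4 to 8 % of a day's milk, and nothing links five single pumpings to formula use. The formula exclusion concerns intent.
- A reader might infer that short samples will be lost. The protocol states discard rules for stool that is not frozen at once or thaws, but no rule that voids a short milk sample. It gives no assay volume, so a smaller aliquot may be quite usable.
- A reader might infer a proven slip of unit from the instruction "The amount of stool should fill the tube between the 5 and 10 ml mark". That tube is for stool, and the milk section says parents receive supplies for that collection. A slip is possible, but the text does not show it.

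**Conclusion.** The point holds as a wrong operating figure in a home-collection instruction. Under an assumed 400 to 1500 mL/day, evenly split and steadily refilled, one breast provides about 17 to 125 mL in the stated interval. The 355 mL requested is about 2.8 to 21 times that. Even with eight hours of refill the request implies about 2.1 L/day. The accurate statement is that the volume or unit is implausible for nearly all mothers, not that no mother could ever reach it.

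The consequence is limited but real. Mothers who try to comply must pool breasts or sessions. Doing so undoes the one-breast, 2–4 hour standardisation of samples meant for the milk-to-stool correlation and the exclusive-breastfeeding check, and diverts milk from the infant on those days. The primary endpoint is not directly affected. This should be corrected, but it does not threaten the trial's main result.

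**What to change.** The Trial status section says recruitment has not begun, so the line can be corrected before any sample is taken.

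- Reconcile the volume, the unit and the tube size in the Breast milk collections section with what the oligosaccharide assay and banking need.
- State that the aliquots are filled from whatever one breast yields at the stated interval, and that a short volume is accepted and recorded. This keeps the sampling conditions the same for every mother and removes the reason to pool.

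The cost is one line in the protocol and the parent sheet, and some smaller banked aliquots. No extra visits or samples are needed.
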